#### Per protocol (PP) analysis set

The PP analysis set consists of the subset of participants who completed the 48-week treatment period and do not have an important protocol deviation.

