### Adherence and protocol deviations

#### Definition of adherence

Study drug treatment adherence for each visit interval is defined as taking at least 80% of the required study drug dosage. For each participant, this will be based on the percentage compliance calculated as: percent compliance = (number of capsules taken by the participant/number of capsules the participant should have taken) *100%. In this study, the participants will be taking four capsules twice a day.

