#### Definition of protocol deviations

Protocol deviations, “any change, divergence, or departure from the study design or procedures in the protocol [2]”, are defined according to the International Conference on Harmonisation of Technical Requirements for Registration of Pharmaceuticals for Human Use (ICH) guideline E3 on Structure and Content of Clinical Study Reports July1996 [6], classified as either “important” or “non-important”. Important protocol deviations are deviations that may significantly impact the completeness, accuracy, and/or reliability of the study data or that may significantly affect a subject’s rights, safety, or well-being. Non-adherence as defined in “Definition of adherence” section will be considered an important protocol deviation. Deviations that do not fit this definition are non-important.

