### Analysis methods

#### Primary analyses

##### Main analysis model

The main analysis will be based on the ITT analysis set. The analysis model will be a linear mixed effects model with endpoint UACR (log-transformed) as the outcome, a categorical variable indicating the allocated grouping structure (intervention versus placebo) as the exposure, and a random effect term to account for the study centre variability. The model will incorporate other covariates as discussed in “Covariate adjustment” section. The results from this analysis will be summarised in Table 3.

**Table 3 Tab3:** Primary and secondary results of the GKT137831 trial

Outcome		Analysis	Mean (standard deviation)		Estimated mean difference^a^	95% Confidence Interval	*P* value
			Intervention (GKT137831) group (n = xxx)	Placebo group (*n* = xxx)			
Primary	Endpoint UACR	Intention to treat (ITT)					
		modified ITT					
		Per protocol (PP)					
Secondary	Midpoint UACR	Intention to treat (ITT)					
		modified ITT					
		Per protocol (PP)					
	Endpoint eGFR	Intention to treat (ITT)					
		modified ITT					
		Per protocol (PP)					
	Midpoint eGFR	Intention to treat (ITT)					
		modified ITT					
		Per protocol (PP)					

*UACR*  urine albumin: creatinine ratio, *eGFR* estimated glomerular filtration rate

^a^ In the intervention group compared to placebo

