##### Additional analyses

Supplementary analyses will be completed by repeating the main analysis described in “Main analysis model” section - “Sensitivity analyses” section using (1) the modified ITT and (2) the PP analysis sets, and these results will be reported in the proposed format.

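### The per-protocol set is only partly tied to whether endpoint UACR reflects assigned treatment, because deviations touching only a participant's rights, safety or well-being also exclude

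*SAP article*

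**What the plan says.** All references are to the SAP article.

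- **Per protocol (PP) analysis set** gives the membership rule in full as follows: "The PP analysis set consists of the subset of participants who completed the 48-week treatment period and do not have an important protocol deviation". The type of important deviation is not restricted.
- **Definition of protocol deviations**, first alternative: "Important protocol deviations are deviations that may significantly impact the completeness, accuracy, and/or reliability of the study data". The sentence continues with a second alternative: "or that may significantly affect a subject’s rights, safety, or well-being". The section adds: "Non-adherence as defined in “Definition of adherence” section will be considered an important protocol deviation".
- **Definition of adherence** sets the threshold used above: "Study drug treatment adherence for each visit interval is defined as taking at least 80% of the required study drug dosage".
- **Presentation of protocol deviations:** the important/non-important split is used to count and describe deviations by arm, without testing.
- **Role of the PP set:** under Main analysis model, "The main analysis will be based on the ITT analysis set". Additional analyses then repeats that work "using (1) the modified ITT and (2) the PP analysis sets, and these results will be reported in the proposed format", and Secondary analyses carries this over to the secondary outcomes. Table 3 has a PP row for the primary outcome and for each of the three secondary outcomes.

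**The concern.** The definition of an important deviation comes from a guideline on clinical study reports. It suits that purpose: a serious lapse in a participant's rights or safety must be reported whether or not it touches the endpoint. The PP section reuses the same class, unfiltered, as an exclusion rule for efficacy analyses. That is a different purpose, because a rights-only lapse says nothing about whether endpoint UACR reflects the treatment assigned.

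What is at stake is the meaning of the PP rows in Table 3, which readers will set beside the ITT rows. Some participants who took treatment as planned and were measured properly may be missing from the PP rows for unrelated reasons. Deviations in the safety limb might also follow adverse events and so differ by arm, which would make the exclusion informative. That is a possibility only, since the article gives no rates.

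**Working it through.** The plan states no figure on this point, so there is none to reproduce. The check is first one of logic, then of size.

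**1. Each PP criterion set against the purpose of an efficacy set**

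| PP criterion | Where stated | Bears on exposure or UACR/eGFR measurement? |
|---|---|---|
| Completed 48 weeks of treatment | Per protocol (PP) analysis set | Yes |
| No non-adherence (under 80% in a visit interval) | Definition of adherence; Definition of protocol deviations | Yes |
| No important deviation, data limb | Definition of protocol deviations | Yes, where the data concerned are dosing, UACR or eGFR |
| No important deviation, rights/safety/well-being limb | Definition of protocol deviations | Not necessarily |

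The two limbs are joined by *or*, so the fourth row excludes on its own.

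**2. A test case**

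Take a participant who completes 48 weeks, meets the 80% threshold in every interval and gives all 4 + 4 = 8 baseline and endpoint first-void samples (Primary outcome measure). Suppose the only important deviation concerns rights, such as a serious lapse in the consent procedure. The first three rows are met and the fourth is not, so the participant leaves the PP set. Nothing else in the article narrows the rule.

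**3. Size, under an assumption**

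Inputs: 60 per arm reaching the end of treatment (Sample size), and a fraction *f* removed only through the fourth row. The article does not give *f*; 5%, 10% and 20% are assumed. With the same *f* in both arms and unchanged residual variance, the number left per arm is 60 × (1 − *f*), and the standard error is multiplied by 1/√(1 − *f*).

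| *f* (assumed) | Lost per arm | Left per arm | Standard error multiplier |
|---|---|---|---|
| 5% | 3 | 57 | 1/√0.95 = 1.026 |
| 10% | 6 | 54 | 1/√0.90 = 1.054 |
| 20% | 12 | 48 | 1/√0.80 = 1.118 |

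The multiplier depends only on *f*. The counts would be smaller if fewer than 60 per arm otherwise qualified.

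**4. Power, for context only**

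The Sample size inputs are means of 13.56 and 13.56 − 3.56 = 10.00, SD 7.5 and correlation 0.3.

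- Lognormal conversion gives log-SDs √ln(1 + (7.5/13.56)²) = 0.517 and √ln(1 + (7.5/10)²) = 0.668.
- The root mean square of these is 0.597, or 0.597 × √(1 − 0.3²) = 0.570 after baseline adjustment.
- The log difference is (ln 13.56 − 0.517²/2) − (ln 10 − 0.668²/2) = 0.394.
- Power is Φ(0.394/(0.570 × √(2/n)) − z), with z = 1.960 two-sided or 1.645 one-sided at 5%.

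| n per arm | Two-sided | One-sided |
|---|---|---|
| 60 | 97% | 98% |
| 57 | 96% | 98% |
| 54 | 95% | 97% |
| 48 | 92% | 96% |

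The 60-per-arm result agrees with the plan's statement of more than 90%. Other conversions to the log scale give lower absolute power, so this table shows only that the loss is modest.

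**The case against.** The strongest reply is that the PP analysis is supplementary. ITT is the main set, modified ITT is reported as well, and no choice of PP rule can alter the primary inference. Excluding all important deviations is also a plain, reproducible rule, whereas filtering by type brings in judgement. The second limb has a threshold too: the effect must be potentially significant, and the article does not say that any particular consent or reporting lapse meets it. Nor does it say that the gap between ITT and PP is to be read as an effect of adherence. All of this stands, and it keeps the point minor. It does not remove the point, because the limb as written needs no link to exposure or measurement.

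Two stronger readings are tempting, and the article supports neither.

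- **That PP membership has no connection with UACR validity.** Completion, the adherence threshold and the data limb all bear on it. Only the remaining limb need not.
- **That the PP set wrongly keeps participants whose background medication changed during the trial.** Eligibility criteria speaks only of changes within 13 weeks before screening. The on-trial rules are in a protocol that is not at hand. A prohibited change could already fall under the data limb, and a participant with a permitted change was still treated per protocol. Excluding for such changes would also select on a post-randomisation event that treatment might influence.

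**Conclusion.** The point holds in limited form. PP membership is partly tied to whether endpoint UACR reflects assigned treatment, and the rights/safety/well-being limb loosens that tie by allowing exclusions unrelated to exposure or measurement. This follows from the article's own definitions and needs no outside figure.

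The size is unknown. The rise of about 3% to 12% in the PP standard error rests wholly on the assumed 5% to 20%, equal loss in both arms and unchanged variance. The cost is mainly to interpretation of the PP rows in Table 3, and only slightly to precision. This is a minor improvement to a supplementary analysis.

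**What to change.** Amend the Per protocol (PP) analysis set section so that an important deviation excludes only if it is judged, blind to allocation and before database lock, to affect exposure to the assigned treatment or the measurement of UACR or eGFR. Name the kinds that qualify: non-adherence, wrong treatment dispensed, and eligibility failures that bear on albuminuria. Keep the completion requirement. Report all other important deviations as Presentation of protocol deviations already provides, and keep those participants in the PP set. Do not add an exclusion for on-trial medication changes.

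The cost is a short change of wording and a blinded classification of deviations that are being logged anyway. The downside is that the classification calls for judgement, which is why it must be finished before unblinding. The ITT primary analysis is not touched.

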## Trial population

### Screen data

At enrolment, the following summaries will be presented by study centre and overall for all screened participants: number of participants screened, the number of recruited participants, the number of screened and eligible participants who are not recruited, the reason for non-recruitment, and the number of recruiting days.

### Eligibility criteria

Participant inclusion and exclusion criteria are presented in Tables 2 and 3 of the protocol [2], respectively. The participants with type 1 diabetes mellitus need to have persistent albuminuria, documented abnormal UACRs in the preceding 24 months before enrolment in the trial, already be receiving standard of care therapy for albuminuria, and have well-controlled blood pressure and HbA1c. Participants are excluded if there is occurrence within 13 weeks before screening of recent changes in medications that may alter albumin excretion or eGFR, or certain procedures that may potentially affect kidney function, or acute kidney injury.

### Recruitment

The trial profile will be illustrated using a flow diagram based on the Consolidated Standards of Reporting Trials) 2010 (CONSORT) [7] as shown in Fig. 1. The following information will be provided in the diagram summarizing the number of participants who are eligible at screening, not eligible at screening (with reasons provided), eligible and randomised, eligible but not randomised (with reasons provided), received the randomised allocation, did not receive the randomised allocation (with reasons provided), withdrawals/lost to follow-up (with reasons provided - see “Withdrawals/follow-up” section), randomized and included in the primary analysis, and randomised and excluded from the primary analysis (with reasons provided).

### Withdrawals/follow up

The number of participants at each level of withdrawal will be documented and the timing of withdrawals will be presented in the CONSORT diagram in Fig. 1, categorized as (1) withdrawn from the intervention but continued with follow up, (2) withdrawn from follow up but allowed data collected to date to be used, (3) withdrawn from follow up and withdrawn consent for data collected to date to be used, and (4) lost to contact/follow up.

### Baseline participant characteristics

The characteristics of the participants, will be summarised by study arm and overall at baseline using summary statistics as shown in Table 2. Continuous variables will be summarised by the appropriate central tendency and dispersion measures, using either mean and standard deviation (SD) or median and 25th–75th percentile. Categorical data will be summarised using frequencies and percentages. The frequencies and percentages of missing values will be reported for all variables.

**Table 2 Tab2:** The baseline characteristics of the participants by intervention, placebo groups and overall

Baseline characteristic	Intervention (GKT137831) group (*n* = xxx)		Placebo group (*n* = xxx)		Percentage standardised difference	Overall (*n* = xxx)	
	Values	Missing, *n* (%)	Values	Missing, *n* (%)		Values	Missing, *n* (%)
**Urine albumin–creatinine ratio (UACR)** (log-transformed)							
Mean (standard deviation (SD))							
**Estimated glomerular filtration rate (eGFR)** (log-transformed)							
Mean (SD)							
**Gender**							
Male, *n* (%)							
Female, *n* (%)							
**Age** (years),							
Mean (SD)							
**Ethnicity**							
xx, *n* (%)							
Other, *n* (%)							
**Clinical variables**							
Systolic blood pressure (mmHg), mean (SD)							
Diastolic blood pressure (mmHg), mean (SD)							
Use of angiotensin-converting-enzyme inhibitor (ACEi), *n* (%)							
Use of angiotensin II receptor blocker (ARB), *n* (%)							
Body mass index (kg/m^2^), mean (SD)							
Duration of diabetes mellitus at baseline (years), mean (SD)							
Glycated haemoglobin (HbA1c %), median (25th–75th percentile)							

## Analysis

### Outcome definitions

The outcome measures of the GKT137831 trial can be divided into primary, secondary, exploratory, pharmacokinetics, and safety outcome measures. This document focuses on the primary, secondary, exploratory, and safety outcomes. Pharmacokinetics assessments will be reported elsewhere.

#### Primary outcome measure

The primary outcome measure of the trial is the urinary albumin excretion level measured by the urine albumin–creatinine ratio (UACR) in milligrams per millimole at the end of the treatment (endpoint UACR), and is defined as the geometric mean of four UACR values, which consists of the two consecutive, daily, first void UACR values at 46 weeks of treatment and the two consecutive, daily, first void UACR values at 48 weeks of treatment. Baseline UACR is defined as the geometric mean of four UACR values, which consists of the two consecutive, daily, first void UACR values at 2 weeks before randomisation and the two consecutive, daily, first void UACR values at randomisation. In the statistical analyses, endpoint UACR will be adjusted for baseline UACR (see “Primary hypothesis” section).

#### Secondary outcome measures

The secondary outcome measures of the trial are the following:

##### Midpoint urine albumin–creatinine ratio

The urinary albumin excretion level at the midpoint of the treatment period measured by the urine albumin–creatinine ratio (midpoint UACR), defined as the geometric mean of the two consecutive, daily, first void UACR values taken at the midpoint of treatment at 24 weeks of treatment.

##### Endpoint estimated glomerular filtration rate

The eGFR at the end of the treatment period at 48 weeks, measured in millilitres per minute relative to body surface area (endpoint eGFR), and is defined as the geometric mean of eGFR at week 46 of treatment and the eGFR at week 48 of treatment. Baseline eGFR is defined as the geometric mean of the eGFR at 2 weeks before randomisation and the eGFR at randomisation.

##### Midpoint estimated glomerular filtration rate

The eGFR at the midpoint of the treatment period at 24 weeks, measured in millilitres per minute relative to body surface area (midpoint eGFR), and is defined as the log-transformed eGFR values obtained at week 24 of treatment.

#### Exploratory outcome measures

The exploratory outcome measures obtained at the end (at 48 weeks) of the treatment period are presented in Sect. 4.2.5 of the protocol [2] and are summarised in Supplementary Table 1. In the statistical analyses, the endpoint exploratory outcome measures will be adjusted for their baseline values taken at randomisation (see “Exploratory analyses” section).

#### Safety outcome measures

The key safety outcome measures are treatment-emergent adverse events and abnormal laboratory analytes as defined in the protocol [1] Sect. 10.4.4.2 and 10.4.4.3, respectively. All safety outcome measures are given in Supplementary Table 2 along with references to the sections where they are defined in the protocol [1].

### Hypotheses

#### Primary hypothesis

The null hypothesis is that the population mean of the endpoint UACR in the intervention group is the same as that in the placebo group (after adjustment for baseline UACR). The alternative hypothesis is that the population mean of the endpoint UACR is lower in the intervention group, compared to that in the placebo group (after adjustment for baseline UACR*)*.

#### Secondary hypotheses

##### Midpoint urine albumin–creatinine ratio

The null hypothesis is that the population mean of the midpoint UACR in the intervention group is the same as that in the placebo group (after adjustment for baseline UACR). The alternative hypothesis is that the population mean of the midpoint UACR is lower in the intervention group, compared to that in the placebo group (after adjustment for baseline UACR).

##### Endpoint estimated glomerular filtration rate

The null hypothesis is that the population mean of the endpoint eGFR in the intervention group is the same as that in the placebo group (after adjustment for baseline eGFR). The alternative hypothesis is that the population mean of the endpoint eGFR is higher in the intervention group, compared to that in the placebo group (after adjustment for baseline eGFR).

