### Randomisation

The randomisation ratio is 1:1 between the active drug (GKT137831) and placebo control arms, and is stratified by study centre and urinary albumin–creatinine ratio (UACR) level with the grouping defined as ≤ 35 mg/mmol or > 35 mg/mmol in female participants and ≤ 25 mg/mmol or > 25 mg/mmol in male participants using a minimisation strategy [4]. Participants will be randomised using a minimisation program integrated into the Interactive Web Response System, and is accessed live by sites through the website Randomize.net (see Sect. 3.3 of the protocol [2]).

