##### Midpoint estimated glomerular filtration rate

The null hypothesis is that the population mean of the midpoint eGFR in the intervention group is the same as that in the placebo group (after adjustment for baseline eGFR). The alternative hypothesis is that the population mean of the midpoint eGFR is higher in the intervention group, compared to that in the placebo group (after adjustment for baseline eGFR).

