##### Covariate adjustment

The main analysis model described in “Main analysis model” section will include (log-transformed) baseline UACR as a covariate. To assess potential baseline covariate imbalance, the participant characteristics at baseline described in “Baseline participant characteristics” section will be compared between the intervention and placebo arms. Instead of using hypothesis testing for this purpose due to its dependence on sample size and emphasis on statistical significance, the standardized differences in means or proportions [8] will be used. The main analysis model will also include the baseline variables that have values of 10% or greater, in the magnitude of the percentage standardised differences, as covariates*.*

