##### Sensitivity analyses

The results obtained by using a mixed effects model of the (log-transformed) endpoint UACR with the allocated grouping structure as the exposure, a random effect term to account for the study centre variability, only incorporating (log-transformed) baseline UACR as a covariate without additional baseline covariates will also be made available. In addition, the sensitivity of the results to the decisions made in constructing the imputation model, will be investigated using visualisations of the distributions of imputed and observed values, standard regression diagnostics [17], and comparisons with complete case analysis. The results will be presented as outlined in Fig. 2.

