#### Secondary analyses

The analyses described in “Main analysis model” section - “Additional analyses” section will be repeated:
For the secondary outcome measures defined in “Secondary outcome measures” section, andUsing the subsets of the GKT137831 group who have taken the 800 mg/day drug for (a) > 6 months and (b) > 12 months as the intervention group for all primary and secondary outcomes defined in “Primary outcome measure” section and “Secondary outcome measures” section, respectively.

The results will be reported in the proposed format.

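### The SAP names different baseline covariates for the eGFR models in different sections and never fixes baseline eGFR and baseline UACR together

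*SAP article*

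**What the plan says.** Five parts of the SAP article bear on the eGFR models.

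- **Secondary hypotheses.** For endpoint eGFR the alternative reads: "population mean of the endpoint eGFR is higher in the intervention group, compared to that in the placebo group (after adjustment for baseline eGFR"). For midpoint eGFR it reads: "population mean of the midpoint eGFR is higher in the intervention group, compared to that in the placebo group (after adjustment for baseline eGFR"). Neither mentions baseline UACR.
- **Secondary analyses.** The eGFR models have no specification of their own. The group of primary analyses, from the main model to the additional analyses, "section will be repeated", first of all "For the secondary outcome measures defined in" the secondary outcomes section.
- **Main analysis model and Covariate adjustment.** The model being repeated has "a random effect term to account for the study centre variability" and "will include (log-transformed) baseline UACR as a covariate". It also takes in any baseline characteristic whose standardised difference between arms is 10% or more in size. Table 2 lists log UACR and log eGFR among those characteristics.
- **Sensitivity analyses.** The reduced model, which is also repeated for eGFR, is described as "only incorporating (log-transformed) baseline UACR as a covariate without additional baseline covariates".
- **Randomisation.** Allocation by minimisation "is stratified by study centre and urinary albumin–creatinine ratio (UACR) level", with sex-specific cut-offs of 35 mg/mmol for women and 25 mg/mmol for men.

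**The concern.** The hypotheses and the repeated models each name one baseline covariate for eGFR, and they name different ones. For the UACR outcomes the two agree: the hypothesis and the model both name baseline UACR, so the allocation factor is always represented. For eGFR a reader has to decide whether the own-outcome baseline takes the place of baseline UACR or is added to it, and the SAP does not say.

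Two of the three secondary hypotheses concern eGFR. They are tested one-sided at 5% with a Benjamini-Hochberg adjustment. Two analysts who follow the SAP in good faith could fit different models and report different p values, which a plan published in advance is meant to prevent. If UACR is dropped, the model also leaves out a factor that the allocation was designed to balance. The reported standard error may then be larger than it needs to be.

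**Working it through.** **Plan's own figure.** The SAP gives no power, standard deviation or correlation for eGFR, so there is no eGFR figure to reproduce. Its power statements concern log UACR and have no bearing on this point.

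**Step 1: set the readings side by side.**

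| Reading | Main eGFR model, fixed terms | Reduced sensitivity model |
|---|---|---|
| Own baseline replaces UACR (natural) | log baseline eGFR, centre | log baseline eGFR, centre; UACR never enters |
| Own baseline added to UACR | log baseline eGFR, log baseline UACR, centre | conflicts with the word limiting that model to baseline UACR |
| Primary model copied unchanged | log baseline UACR, centre | log baseline UACR, centre; conflicts with the hypotheses |

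The first reading fits best. The hypotheses adjust each outcome for its own baseline throughout, and the exploratory and safety sections follow the same rule. The Outcome definitions section defines a baseline eGFR, which would otherwise have no clear use. Under this reading centre is still represented, as a random effect, but UACR level is not.

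**Step 2: size of the loss under the natural reading.** Let r be the partial correlation of baseline log UACR with follow-up eGFR, given baseline eGFR. The documents do not give r, so a range is assumed. Leaving UACR out multiplies the residual variance by 1/(1 − r²) and the model standard error by 1/√(1 − r²). The equivalent sample size out of the 120 planned completers is 120 × (1 − r²).

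| Assumed r | 1 − r² | SE increase | Equivalent N of 120 | Power if 90% when adjusted (one-sided 5%) |
|---|---|---|---|---|
| 0 | 1.00 | 0% | 120 | 90.0% |
| 0.1 | 0.99 | 0.5% | 118.8 | 89.7% |
| 0.2 | 0.96 | 2.1% | 115.2 | 88.9% |
| 0.3 | 0.91 | 4.8% | 109.2 | 87.4% |

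The power column is Φ((1.645 + 1.282) × √(1 − r²) − 1.645). For r = 0.3 this is Φ(2.927 × 0.954 − 1.645) = Φ(1.147) = 87.4%. The 90% is only a reference point, since the SAP claims no power for eGFR.

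**Step 3: simulation.** The set-up was 120 participants, minimisation on 15 assumed centres and a two-level UACR stratum, and 3,000 runs per r. A correlation of 0.8 between baseline and later eGFR was assumed. Ordinary least squares was used without the centre effect.

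- The reported SE without UACR, relative to the SE with it, was 1.003, 1.019 and 1.046 for r = 0.1, 0.2 and 0.3.
- The true spread of the estimate rose less: 1.000, 1.010 and 1.021. Part of the larger SE is therefore lost precision, and part is an SE that overstates the true error.
- The one-sided type I error without UACR was 0.046, 0.046 and 0.043, against 0.047, 0.048 and 0.048 with it. The Monte Carlo error is about 0.004. The direction is conservative and the difference is small.

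**Step 4: would the 10% rule restore UACR?** With 60 per arm and no balancing, the standardised difference has standard error √(2/60) = 0.183. It reaches 10% in size with probability P(|Z| > 0.10/0.183 = 0.55), about 58%. In the simulation, with minimisation on the stratum, log UACR entered in about 40% of trials. The rule therefore leaves its inclusion to chance and to the observed data.

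**The case against.** The strongest reply is that there is no real contradiction. The hypotheses are not covariate lists: the primary one also omits centre and the imbalance covariates, yet the model includes them. Silence about UACR in the eGFR hypotheses therefore does not remove it. If baseline eGFR comes from the hypotheses and baseline UACR from the repeated model, the result is the model asked for here.

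That reading is possible, and it means that omission of UACR is not established. But the SAP does not state it, and the sensitivity model, limited to baseline UACR, cannot be combined with the hypotheses in that way. The ambiguity stands.

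A reader might infer three stronger points, which the document does not support.

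- **That the eGFR models drop baseline eGFR.** An unchanged copy of the primary model would do so. With an assumed baseline-to-endpoint correlation of 0.7 to 0.9, the residual variance would be 1/(1 − r²) = 1.96 to 5.26 times larger. But both eGFR hypotheses expressly adjust for baseline eGFR, so this reading contradicts the text.
- **That precision is certainly lost.** The loss depends on a correlation that the SAP does not give. It is nil at r = 0, and the 10% rule may restore UACR.
- **That the test has a definite size below 5%.** The formula P(Z > 1.645/√(1 − r²)) gives 4.9%, 4.7% and 4.2% for r = 0.1, 0.2 and 0.3, but only if continuous UACR were fully balanced. The Randomisation section balances a two-level category. If the planning mean of 13.56 and SD of 7.5 described a lognormal baseline (an assumption), the log SD would be √ln(1 + (7.5/13.56)²) = 0.517 and the log mean ln 13.56 − 0.517²/2 = 2.474. About 7% of men would then lie above 25 (z = 1.44) and about 2% of women above 35 (z = 2.09). Such a category balances little of the continuous variable.

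**Conclusion.** The point holds as an inconsistency in the covariate set for endpoint and midpoint eGFR. The hypotheses name baseline eGFR, the repeated main and sensitivity models name log baseline UACR, and no section fixes both. On the natural reading UACR is left out unless the imbalance rule adds it.

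The consequence is small: a standard error about 0.5%, 2% or 5% larger for assumed partial correlations of 0.1, 0.2 or 0.3, none at 0, and at most a slightly conservative test. These figures rest on the assumed correlations and on 120 completers. Type I error is not inflated, and the primary UACR analysis is unaffected. The severity is minor. Because the remedy costs almost nothing and follows the allocation scheme, it is a free improvement.

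**What to change.** In Covariate adjustment, Sensitivity analyses and Secondary analyses, state: for endpoint and midpoint eGFR, every model, including the reduced sensitivity model, contains log baseline eGFR and log baseline UACR as fixed covariates with the random centre effect, whatever the observed imbalance. The two-level allocation stratum could stand in for log baseline UACR; the SAP should say which is used. In the two eGFR hypotheses, name both covariates in the bracketed adjustment.

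Both baseline values are already defined under Outcome definitions, so no new data are needed. Compared with a model holding baseline eGFR alone, the cost is one degree of freedom per model and a few words in the SAP.
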